#### **7.3.4.3 Drug Compliance**

The first dose of each course will be given under supervision of study staff and the remaining 2 doses for days 2 and 3 will be taken at home by the study women. Women will be reminded through mobile phone contact to take the assigned tablets for the second and third dose. A sub-sample of women will be visited at home by random spot checks (some on Day 2 and other women on Day 3, with Day 1 being the first day of treatment) to assess adherence to the study drugs. In our previous trial in western Kenya documented adherence using this method was very high (>95%).

### **7.3.5 Removal of participants from study**

#### **7.3.5.1 Removal of participants from therapy and/or assessment**

Participants can discontinue from the study for any one of the following reasons:

1. Screening error resulting in incorrect enrolment (found that subject did not meet required inclusion / exclusion criteria)
2. Withdrawal of consent at any stage or subject not willing to continue in the study
3. Suspected or confirmed allergic reaction to the study drug (removal from therapy only)
4. Safety reasons as judged by the investigator, study safety monitor or DMEC (removal from therapy only)

Where feasible, the participants who discontinue from the study treatment or from the study entirely will be asked about the reason(s) for their discontinuation and the presence of adverse events. Participants have the right to unconditionally withdraw from participation in the study without providing a reason. If a subject discontinues, data captured will contribute to the analysis up to the day prior to discontinuation, unless the subject indicates that she withdraws consent for any data captured up to that point. Every effort will be made to follow-up participants who discontinue due to drug related adverse events to determine the birth outcome. If a subject discontinues due to drug-related adverse events, all the assessments that would have been carried out at the next scheduled visit will be conducted at day 28 where reasonably possible (unless consent is withdrawn). This will be recorded in the CRFs. The study drug will be returned by the subject. Subjects that have discontinued the study prematurely will not be replaced.

### 7.3.5.2 Discontinuation from storage of samples for future studies

The applicability of long term storage of study samples for future research shall be in respect to the regulations of the country specific ethics board. When a subject's consent for long-term storage is withdrawn, the stored sample will be destroyed and the withdrawal noted in the CRF. If the request is received after the dataset has been anonymised, the stored sample can no longer be withdrawn.

## 7.4 OUTCOMES

### 7.4.1 Primary outcome

#### Adverse pregnancy outcome

The primary outcome is 'Adverse pregnancy outcome' defined as the composite of foetal loss (spontaneous abortion or stillbirth), or singleton live births born small-for-gestational age (SGA), or with low birthweight (LBW), or preterm (PT) (SGA-LBW-PT), or subsequent neonatal death by day 28. Small for gestational age will be defined using the new INTERGROWTH population reference's 10th percentile.

### 7.4.2 Key secondary outcome measures

#### 7.4.2.1 efficacy

1. Composite of foetal loss and neonatal mortality
2. SGA-LBW-PT composite
3. The individual components of the above composites newborn outcome both as categorical and continuous variables
4. Neonatal length and stunting
5. Clinical malaria during pregnancy
6. Malaria infection during pregnancy detected by microscopy and PCR (not for point of care)
7. Placental malaria detected by microscopy, by molecular methods or by histology (past and active infection)
8. Individual components of the placental malaria composite
9. Maternal nutritional status
10. Maternal anaemia and haemoglobin concentration during pregnancy and delivery
11. Congenital anaemia
12. Congenital malaria infection

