| 
Visit 1: Pre-screening interview, Screening, Consent, Enrolment, Randomisation, and Allocation. First IPTp treatment dose given under direct observation.
 
Visits 2 to 4: Monthly IPTp treatment and ANC follow-up visits.
 
Visit 5: Delivery visit. To be conducted as soon as possible after birth without interrupting the initiation of breastfeeding or any necessary care required to the mother or newborn. A surface examination shall be conducted to assess for external congenital abnormalities.
 
Visits 6 and 7: Routine postnatal care, physical examination and follow-up of the mother-newborn pair.
 
a. Visits spaced approximately one month apart. The max. number of scheduled visits depends on the gestational age at enrolment (estimated median of 3 to 5).
 
b. Pre-study screening can take place any time women start visiting the ANC; i.e. even prior to 16 weeks gestation, but the intervention can only start at 16 weeks.
 
c. Cardiac safety monitoring; One ECG prior to 1st dose of each course and one 4-6 hours after the 3rd dose of each course (subgroup 160 women, 80 in each DP arm).
 
d. The first dose (day-0) always given under direct observation and subsequent 2 doses are to be taken at home (day-1 and day-2).
 
e. Baseline ultra sound scans in all women to assess the gestational age. Additional ultrasound scans to determine foetal growth at scheduled visits occurring at the approximate gestational ages of 25-28 weeks and 32-35 weeks (subgroup only), or otherwise at the nearest scheduled monthly visit.
 
f. Vomiting and other adverse events (AEs) occurring within 30 minutes of the first dose will be assessed. Subsequent AEs will be captured though passive surveillance. Participants will be encouraged to report to the study clinic for any subsequent AEs that may arise after each study visit at any time before the next study visit.
 
g. Enrolment & delivery blood sample by venepuncture (VP) (up to 10 mL) or finger prick (~250µL): All women all sites: haemoglobin level, HIV test (unless known to be HIV+), syphilis, malaria smear, dried blood spots (DBS) for molecular malaria diagnostics (not for point of care, DBS for multi-pathogen antibody assays and drug resistance. Sub-group (venepuncture): Nutritional biomarker including leptin, adiponectin, aflatoxin-albumin adduct (AF-alb) levels; antibody and cell mediated immune responses to malaria and other pathogens; biomarkers of placental function, inflammation and gestational age; malaria diagnostics, and drug levels. Remaining red cell pellets will be stored.
 
h. Interim study visits blood sample by venepuncture (up to 10 mL) or finger prick (~250µL): Same assays as for baseline, with the exception of syphilis. HIV testing and nutritional biomarkers will be done once in third trimester only during one of the last scheduled visits prior to delivery.
 
i. Umbilical cord blood (CB) sample (7 mL in subgroup and 5 mL in all others): Haemoglobin level, malaria molecular diagnostics, antibody and cell mediated immune responses to malaria and other pathogens, and nutritional biomarkers including leptin, adiponectin and drug levels. Heel prick (HP) sample (~ 500 microl) in all babies with fever or other symptoms for malaria RDT, microscopy and dried blood spot, and in subgroup of asymptomatic infants for immunological assays.
 
j. Venepuncture 2 ml blood sample taken 4-6 hours after last dose of each course (cMax) for biochemistry and drug levels (subgroup of 160 women in ECG component)
 
k. Stool sample at enrolment and last scheduled antenatal ANC visit prior to delivery in subgroup (n~1,464). Postnatally, only new-born stool sample shall be collected.
 
l. Placental samples at delivery/termination of pregnancy: placental section for histopathology, amnion roll, placental impression smear, maternal placental blood for malaria diagnostics (not for point of care), drug levels, and cord blood (i.e. newborn's side) (see cord blood sample).
 
m. Maternal anthropometric measurements: Enrolment: height; All visits: Weight, and MUAC. Sub-group only: delivery, 1 and 6-8 postpartum: skinfold thicknesses (SFTs), hip and waist circumference, bioelectrical impedance analysis and deuterium analysis (FTIR).
 |   |   |                |

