#### **7.5.4.3 Umbilical cord sampling**

A 5 mL umbilical cord blood sample will be taken for haemoglobin level, malaria molecular diagnostics, antibody and cell mediated immune responses to malaria and other pathogens, and nutritional biomarkers including leptin, adiponectin, and drug levels. This will be a total of 7 mL for those contributing to the assessment of the impact on immunological outcomes: Maternal antibody, trans-placental antibody transfer and multi-pathogen neonatal cell mediated immune responses (page 88) for the additional assays on cell mediated immune responses involving peripheral blood mononuclear cell (PBMC).

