#### 7.6.1.2 *Sample size for a standalone trial*

The sample size calculations for the standalone trial were conducted using PASS software. The total sample size will be 4,680 women (1,560 per arm) across three countries pooled. A sample size of 4,020 women (1,340 per arm) will achieve 80% power trial to detect a  $\geq 20\%$  reduction in the primary endpoint from 21.3% with IPTp-SP to 17.0% ( $RR=0.80$ ) ( $\alpha=0.05$ ) (90% power to detect a 23.0% reduction). 4,035 (1,345 per arm) women are required to allow for 1 interim analysis using the Lan-DeMets spending function with O'Brien-Fleming type boundaries to preserve the overall two-sided type I error rate for efficacy (see.10.1.3, page 45).

We will recruit 4,680 women (1,560 per arm) to allow for 13.7% loss to follow-up, which is approximately double the rate of loss to follow-up for this same primary composite endpoint in our recently completed MiP trials in Malawi (N=1873, across 2 arms) and Kenya (N=1546, across 3 arms). These trials involved similar sample sizes per country as in the proposed study, however the higher rate of loss to follow-up is used for our current sample size calculations since not all hospitals will have been part of the previous studies.

This same sample size of 1,340 completers per arm also provides 80% power to detect a further 22.8% reduction ( $RR=0.772$ ) from 17.0% in the IPTp-DP alone arm to 13.1% in the IPTp-DP+AZ arm ( $\alpha=0.05$ ) (or 90% power to detect a 26.1% reduction [ $RR=0.739$ ] from 17.0% to 12.6%). The 21.3% primary endpoint prevalence in the control arm is the observed mean prevalence in the IPTp-SP arms of our previous trials in the same sites in Kenya and Malawi, which also provided LLINs on enrolment, and in observational cohort studies in Tanzania.

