### 9.3.2.2 Secondary endpoints analyses

These will also be analysed using GLMs with the treatment arm as the single predictor and country (Kenya, Malawi and Tanzania) and gravidity (pauci and multigravidae) as control variables. The point estimate of the treatment effects with 95% CI will be derived via specification of a GLM model for each secondary outcome depending on its distribution. For a binary outcome such as the components of primary endpoint, similar analysis to the primary endpoint analysis will be performed and the treatment effects measured as RR will be generated. For a continuous outcome like birthweight, a Gaussian distribution will be assumed and identity link function will be used. Correspondingly the mean difference and its 95%CI between two arms will be calculated. For a count outcome such as the number of SAEs, Poisson distribution and log link function will be used, from which incidence rate ratio (IRR) and its 95% CI will be computed.

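### Key secondary outcome 11 names newborn anaemia only as a yes/no outcome, although cord haemoglobin is measured and the maternal item names both forms

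*Protocol*

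**What the plan says.** Section 7.4.2.1 lists twelve key secondary efficacy outcomes. Item 11 is "Congenital anaemia", and the registration table in 2.3.1 repeats it. Item 10 reads "Maternal anaemia and haemoglobin concentration during pregnancy and delivery". Item 3 covers "The individual components of the above composites newborn outcome both as categorical and continuous variables"; this refers to the composites in items 1 and 2, and anaemia belongs to neither.

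The measurement is planned. Section 7.5.4.3 states: "A 5 mL umbilical cord blood sample will be taken for haemoglobin level". Footnote i to Table 1 shows that the sample is not confined to a subgroup: "Umbilical cord blood (CB) sample (7 mL in subgroup and 5 mL in all others): Haemoglobin level".

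The model exists too. Section 9.3.2.2 states: "For a continuous outcome like birthweight, a Gaussian distribution will be assumed and identity link function will be used", which yields a mean difference with a 95% confidence interval. For binary outcomes the same section gives a risk ratio.

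The protocol lists no cord or newborn haemoglobin concentration as an outcome. It gives no rate, standard deviation, expected effect or power for congenital anaemia.

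**The concern.** A yes/no outcome cut from a continuous measurement uses only part of the information in it. Elsewhere the list avoids relying on the cut alone: maternal anaemia is paired with haemoglobin concentration, length with stunting, and the composite components are taken in both forms. Item 11 is the exception, although cord haemoglobin will be in hand and the model for it is already written.

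At stake is the precision of one secondary comparison. A modest effect of DP or DP+AZ on newborn haemoglobin could be missed by the anaemia risk ratio and detected by the mean difference. If haemoglobin concentration were added only after results were known, it would look post hoc. The primary endpoint and the sample size are not affected.

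**Working it through.** **1. The sample size available.** Section 7.6.1.2 states: "A sample size of 4,020 women (1,340 per arm) will achieve 80% power trial to detect" a reduction "in the primary endpoint from 21.3% with IPTp-SP to 17.0"%, a risk ratio of 0.80. With p1 = 0.213, p2 = 0.80 × 0.213 = 0.1704, mean p = 0.1917, two-sided 5% and 80% power:

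n = [1.96·√(2·0.1917·0.8083) + 0.8416·√(0.213·0.787 + 0.1704·0.8296)]² / 0.0426²
= [1.0911 + 0.4678]² / 0.0426² = 1,339.2, rounded up to **1,340 per arm**, as stated.

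Allowing for the interim and dropout, 1,345/(1 − 0.137) = 1,558.5, against 1,560 stated.

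**2. Inputs for newborn anaemia.**
- n = 1,340 per arm: the completers in 7.6.1.2.
- Two-sided 5%: section 9.3.1.
- Control anaemia p1 = 10%, 20%, 30%: assumed.
- Relative reductions of 22% and 13%: section 3.4, for *maternal* anaemia at delivery in Kenya and Uganda. Nothing in the protocol carries them over to newborns, so they too are assumptions here.
- Haemoglobin normal with equal spread, shifted by d standard deviations: assumed.

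**3. Formulas.** With p2 = p1 × risk ratio:
- Yes/no power = Φ((p1 − p2)/√(p1q1/n + p2q2/n) − 1.96)
- Continuous power = Φ(d·√(n/2) − 1.96), where d = Φ⁻¹(p1) − Φ⁻¹(p2)

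**Example, p1 = 20%, risk ratio 0.78.** p2 = 15.6%. Yes/no: 0.044/0.01475 = 2.98, so Φ(1.02) = 84.7%. Continuous: d = 0.1694 and d·√670 = 4.385, so Φ(2.425) = 99.2%. Gain 14.6 points.

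| Control rate | Risk ratio | Shift d (SD) | Yes/no power | Continuous power | Gain (points) |
|---|---|---|---|---|---|
| 10% | 0.78 | 0.137 | 51.7% | 94.4% | 42.7 |
| 20% | 0.78 | 0.169 | 84.7% | 99.2% | 14.6 |
| 30% | 0.78 | 0.201 | 97.2% | 99.9% | 2.7 |
| 10% | 0.87 | 0.078 | 21.1% | 52.3% | 31.2 |
| 20% | 0.87 | 0.097 | 40.8% | 70.8% | 30.0 |
| 30% | 0.87 | 0.116 | 61.4% | 85.1% | 23.7 |

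With 1,000 cord samples per arm (an assumed shortfall, for example from home births) and risk ratio 0.87, the gains are 24.6, 26.2 and 24.3 points.

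**4. Information kept by the cut.** Under the same model the efficiency of a cut at rate p is φ(z)²/(pq): 0.1755²/0.09 = 34% at 10%, 0.2800²/0.16 = 49% at 20%, 0.3477²/0.21 = 58% at 30%.

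**5. When the shift model fails.** Suppose haemoglobin is lowered in only some newborns and treatment cuts that share. With 30% to 50% of pregnancies affected in the control arm, the gain is about 10 to 53 points where continuous power is 50% to 95%, falling to 7 to 9 in a few cases.

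A large drop in a smaller share can reverse it. Take a 3 SD drop in 20% of controls, reduced by 30% to 14%, with a cut that flags 3% of unaffected newborns:
- Continuous: mean difference 0.06 × 3 = 0.18; variances 1 + 0.2·0.8·9 = 2.44 and 1 + 0.14·0.86·9 = 2.08; 0.18/√(4.52/1,340) = 3.10, so power is 87%.
- Yes/no: rates 19.8% and 14.7%, power 93%.

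**The case against.** The strongest reply is that section 7.4.2.1 is a list of outcome names, not an analysis specification. Section 9.3.1 leaves detail to the statistical analysis plan, and 9.3.2.2 lets each secondary outcome's model follow its distribution. The protocol's own labels are also loose: the registration table in 2.3.1 gives the maternal outcome as anaemia alone, while 7.4.2.1 gives the same outcome with haemoglobin concentration. This stands. A reader might infer that the protocol commits to testing the newborn effect by a risk ratio only; the text does not say so. Nor is the missing cut-off a finding, since an analysis plan commonly supplies it.

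The second reply is that the size is assumed, not derived. That stands too. One of the six cells gains only 2.7 points, and a concentrated effect can favour the cut. A reader might conclude flatly that the listing costs well over 5 points of power, or that the cut throws away most of the information. The first depends on inputs the protocol does not give. The second fails in general: the cut keeps about half at a 20% rate and 58% at 30%.

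The third reply is that anaemia is the more tangible outcome and should not be demoted. Agreed. Item 10 ranks neither form, so it gives no precedent for making the mean difference the inferential analysis.

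What the replies do not remove is the gap itself. The list names both forms for mothers and one for newborns, and item 3 does not fill it.

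**Conclusion.** The point holds as a low-cost improvement to one of twelve key secondary efficacy outcomes, not as an analysis error with a known power cost. Item 11 names only the yes/no form of a measurement planned at every delivery, out of line with the maternal item beside it.

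Under a normal shift, 1,340 per arm, control rates of 10% to 30% and relative reductions of 13% to 22%, adding the continuous form gains about 14 to 43 points of power (14.6 to 42.7 in the table), except under 3 points where the yes/no test is already at 97%. The rates and the shift are assumed, and the reductions are borrowed from maternal anaemia. If the effect were a large drop in a small share of newborns, the gain could disappear or turn slightly negative, which is a reason to report both forms.

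**What to change.** In 7.4.2.1 and in the registration table in 2.3.1, change the item to *Congenital anaemia and cord haemoglobin concentration*. Report the mean difference in cord haemoglobin from the Gaussian identity-link model already in 9.3.2.2 alongside the anaemia risk ratio, with neither ranked above the other, as in item 10.

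No new sample, visit, assay or model is needed. The cost is a wording change in two places and one more secondary estimate to report.

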#### 7.4.2.2 Safety

1. QTc-prolongation
2. Congenital malformations
3. Maternal mortality
4. Other SAEs and AEs

#### 7.4.2.3 Tolerance

1. History of vomiting study drug
2. Dizziness
3. Gastrointestinal complaints

#### 7.4.2.3 Antimicrobial activity and resistance

1. Molecular markers of drug resistance in *Plasmodium falciparum* infections during pregnancy and delivery

2. Presence of STIs/RTIs prior to delivery (syphilis, gonorrhoea, *Chlamydia trachomatis*, *Trichomonas vaginalis*, and bacterial vaginosis)
3. Changes in macrolide resistance in *Pneumococcus* detected in maternal nasopharyngeal samples
4. Changes in the colony composition of maternal vaginal microbiota, and intestinal microbiota of mother and infant

## PARTICIPANTS TIMELINE

### 7.5.1 Antenatal booking visit

If a woman makes first contact with the study team between 16 and 28 weeks gestation (inclusive), the first study visit will immediately follow eligibility screening. If a woman makes first contact before 16 weeks gestation, she will be invited to be enrolled into the study at the next clinic visit when she would have reached the eligible gestational age where all screening and enrolment procedures will be conducted. Additional informed consent shall be sought from 160 women (80 per DP intervention arm) for cardiac monitoring and safety evaluation at some sites.

#### 7.5.1.1 Enrolment

After informed consent has been signed, participants will be randomly allocated (see section 8) to receive either IPTp-SP, IPTp-DP, or IPTp-DP+AZ (see section 8, Methods: Assignment of interventions, page 39) and issued with a trial identifier with their unique study identification number.

At this stage study staff will ask the participant for a home or mobile telephone number if they have one, and home address or a description of the location of their home, and for their verbal consent to be visited at home whenever they do not attend scheduled appointments.

#### 7.5.1.2 Baseline assessment

A baseline assessment will be conducted for each participant comprising demographic information, socioeconomic information, ITN and IRS use, medical and obstetric history, and clinical assessment. Any relevant information already collected during the screening process or at previous antenatal appointments for the same pregnancy will be copied from the antenatal cards onto the CRF, so that questions, tests and examinations are not unnecessarily duplicated.

Study-relevant information recorded at the first visit will include age; area of residence; prior use of ITNs; number of previous known pregnancies and number of previous births and corresponding pregnancy outcomes. Clinical assessment will include height and weight, mid-upper arm circumference, fundal height, reported date of last menstrual period and estimated gestation.

#### 7.5.1.3 Biological samples

A venous (up to 10 mL) or finger prick whole blood sample (~250 µL) will be taken and used for both routine and study-specific testing. This will be obtained after consent for eligibility screening has been obtained but before consent for enrolment in the trial; women who have not been tested for HIV in their current pregnancy will be tested for HIV, and all women will be tested for anaemia and haemoglobin levels. Women not previously tested for syphilis in this pregnancy will be tested and treated if positive. The same blood sample will be prepared for study-specific diagnostic testing for malaria (e.g. not for point of care). A filter-paper sample will be prepared and stored for parasite genetic studies.

In a subgroup of 160 women enrolled in the nested cardiac monitoring study in the DP arms, an additional 2 mL of whole blood will be required for drug level assessment, full blood count, biochemistry for electrolytes, liver and renal function test, 4-6 hours after the 3rd dose of DP intervention.

In a subgroup of approximately 1,464 women in selected sites, women will be requested to provide a self-administered vaginal swab and a stool sample at enrolment for baseline reproductive tract and gut microbiota colonisation respectively. If no fresh stool sample can be produced on or just before the day of enrolment, the woman shall be requested to submit the stool sample the following day.

A sub-group of approximately 1,032 women will be asked to provide nasopharyngeal swabs for carriage macrolide resistant *Streptococcus*.

#### **7.5.1.4 Study intervention**

The first course of IPTp will be administered to asymptomatic women at the visit as described in section 7.3.1, Trial Medications and interventions, page 27. If women have symptomatic malaria, they will be treated as described in section 7.3.2.1.: Symptomatic malaria.

